### 2.12. Statistical analysis

An independent statistician will conduct statistical analysis using SAS® Version 9.4 (SAS Institute Inc., Cary, NC). According to principle, an efficacy analysis will be conducted using a full analysis set according to the intention-to-treatment principle, including all randomly assigned participants who received at least 1 evaluation after the investigational product has been prescribed at least once. If necessary, per-protocol set analysis will also be conducted, including only participants who have completed the entire process as described in the protocol and have no significant violations. Participants with < 70% compliance with the investigational product will be excluded from the per-protocol set analysis. The safety analysis will include all data obtained from participants who have taken at least 1 investigational product.

The demographic and general clinical characteristics of the participants will be summarized by grouping. Continuous data will be presented as mean and 95% confidence intervals or medians according to the data distribution, and dichotomous data as frequency and percentage. Continuous data will be analyzed using the independent t-test or Wilcoxon rank-sum test, and dichotomous data will be analyzed using the chi-square test or Fisher exact test.

The primary outcome of this study is the mean change in LDL-C levels from baseline to week 8. A 2-sided test with a significance level of 5% will be performed using an analysis of covariance with baseline as the covariate and the treatment group as the fixed factors. The intragroup changes in outcome measures from baseline to posttreatment will be analyzed using the paired *t* test or Wilcoxon signed-rank test for continuous variables and the chi-square test or Fisher exact test for dichotomous variables. Furthermore, repeated-measures analysis of variance will be used to compare the differences in trends between visits in each group. Missing values will be replaced with the multiple imputation method. If necessary, subgroup analysis can be performed by categorizing the initial characteristics of participants at the screening or baseline visit.

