## 2. Methods

### 2.1. Study design and setting

This is a study protocol for multi-center, randomized, double-blind, placebo-controlled, parallel, investigator-initiated pilot study. Subjects will be recruited from 2 hospitals, Kyung Hee University Oriental Medical Center (Seoul) and Wonkwang University, Gwangju Medical Center (Gwangju), between November 2021 and December 2022. The study period will include 4 weeks of lifestyle modification, 8 weeks of medication, and 4 weeks of follow-up. The study period procedure is summarized in the Consolidated Standards of Reporting Trials (CONSORT) diagram (Fig. 1), and the schedule of enrollment, intervention, and assessments is summarized in Table 1. The trial will be performed in accordance with the Declaration of Helsinki and the Good Clinical Practice Guidelines. This study was sponsored and managed by the Korea Institute of Oriental Medicine (KIOM) during the study period. KIOM wrote the protocol following the CONSORT Extension for Chinese Herbal Medicine Formulas 2017^[22]^ and Standard Protocol Items: Recommendations for Interventional Trials 2013 statement.^[23]^

**Table 1 T1:** Schedule of enrollment, interventions, and assessments.

	Study period					
	Screening		Post allocation			Follow-up
Time point	1st (−4 w)	2nd (±7 d)	Baseline (−14 d)	W 4 (±7 d)	W 8 (±7 d)	W 12 (±7 d)
Enrollment						
Informed consent	●					
Eligibility screen	●					
Demographic characteristics	●					
Medical history	●					
Random allocation			●			
Interventions						
Dietary and exercise education	●	●	●	●	●	
GBH or placebo			← - - - - - - - - - - - - - - - - - - - - →			
Assessments						
Vital sign	●	●	●	●	●	●
Laboratory testing*	●	●		●	●	●
Pregnancy testing		●		●		
Blood stasis questionnaire	●		●		●	
Blinding test					●	
Adverse events			●	●	●	●
Medication compliance				●	●	

GBH = Gyejibongnyeong-Hwan.

* Including hematological test, blood lipid parameters, blood glucose parameter, liver and renal function test, and urine test.

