The use of fibrates, bile acid sequestrants, niacin, anti-obesity drugs, steroids intended for systemic action, fish oil, colestine products, fiber-based laxatives, phytosterol margarine, which can affect the lipid profile, the drugs usage that can affect thyroid function, such as thyroxine, and will be prohibited during the study period.

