### 2.6. Outcomes measures

#### 2.6.1. Primary outcome.

Percentage changes in LDL-C from the baseline to week 8.

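### The supplementary per-protocol set is tied to completing the whole study, including the off-drug week 12 visit, although the primary LDL-C outcome is complete at week 8 (minor)

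*Protocol article*

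**What the plan says.** The primary outcome (Section 2.6.1) is "Percentage changes in LDL-C from the baseline to week 8". Section 2.5 sets 8 weeks of dosing. Section 2.1 extends the study beyond that point: "The study period will include 4 weeks of lifestyle modification, 8 weeks of medication, and 4 weeks of follow-up". Table 1 schedules vital signs, laboratory testing and adverse events at week 12, after dosing has ended.

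Section 2.12 bases efficacy on a full analysis set, "including all randomly assigned participants who received at least 1 evaluation after the investigational product has been prescribed at least once". The per-protocol set is secondary: "If necessary, per-protocol set analysis will also be conducted". Its membership is then restricted by the words "including only participants who have completed the entire process as described in the protocol and have no significant violations". There is also a compliance cut-off: "Participants with < 70% compliance with the investigational product will be excluded from the per-protocol set analysis".

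Section 2.5 lists drugs and products "which can affect the lipid profile" (fibrates, bile acid sequestrants, niacin and others), whose use "will be prohibited during the study period". By Section 2.1 that period includes weeks 8 to 12.

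**The concern.** A per-protocol analysis of a week 8 outcome should describe people who followed the protocol up to week 8. What happens afterwards cannot change a value already drawn, so it should not decide who is analysed. As worded, the completion criterion has no cut-off at week 8. Two kinds of participant with a valid week 8 LDL-C are exposed to removal:

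- one who took the product as required, had the week 8 blood draw and then missed week 12;
- one who started a listed lipid-affecting drug after the week 8 draw, if that were judged a significant violation.

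The first follows directly from the wording and costs information. The second depends on how a violation is graded. If either kind of exclusion happened to be related to the week 8 LDL-C, the per-protocol comparison would be selected on its own outcome. Section 4 says the results will be used to design a confirmatory trial, so a needlessly smaller or attenuated per-protocol estimate could carry forward.

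**Working it through.** **Reading the text.** Per-protocol membership requires completing the process in the protocol (Section 2.12). That process includes 4 weeks of follow-up (Section 2.1) with a scheduled week 12 visit (Table 1). The outcome is fixed at week 8 (Section 2.6.1). Section 2.12 does not name week 12, so its inclusion is an inference from these places, but nothing in the article ends the process at week 8.

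The article gives no figure for exclusions after week 8, so there is none to reproduce. The sizes below rest on stated assumptions.

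**Precision.** Inputs: 90 participants and 20% dropout (Section 2.8). Assumption: dropout is spread evenly over the 12 weeks from randomisation.

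- Expected dropouts: 0.20 × 90 = 18.
- Falling in weeks 8 to 12: 18 × 4/12 = 6.
- Reaching week 8: 90 − 12 = 78. Reaching week 12: 90 − 18 = 72.
- Ratio of standard errors: √(78/72) = 1.041, an increase of about 4%.

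Compliance exclusions are ignored here.

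**Selection, worst case.** Assumptions: normal outcome in SD units, true difference d = 0.20 SD (the effect size in Section 2.8), and everyone above a common response threshold c, and no one below it, is removed after week 8. Removing the upper tail lowers an arm's mean by φ(c)/Φ(c) for placebo and by φ(c + d)/Φ(c + d) for GBH. The remaining difference is d minus the gap between these two shifts.

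| Placebo removed | c | GBH removed | Shift, placebo | Shift, GBH | Difference left | Loss |
|---|---|---|---|---|---|---|
| 5% | 1.645 | 3.3% | 0.109 | 0.075 | 0.167 | 17% |
| 10% | 1.282 | 6.9% | 0.195 | 0.143 | 0.148 | 26% |
| 20% | 0.842 | 14.9% | 0.350 | 0.272 | 0.122 | 39% |

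**Selection, partial uptake.** Here only a fraction of those in the worst third (cut at the placebo 2/3 quantile) is removed, by the same rule in both arms. Results are by simulation with 2,000,000 per arm; the closed form agrees to within 0.001 at d = 0.20.

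| Removed from worst third / from others | Placebo removed | GBH removed | Difference left (true 0.20) |
|---|---|---|---|
| 10% / 0% | 3.3% | 2.6% | 0.195 |
| 30% / 0% | 10.0% | 7.9% | 0.186 |
| 50% / 5% | 20.0% | 16.9% | 0.173 |

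The loss is about 2% to 14%. At a true difference of 0.50 SD the same rules leave 0.488, 0.460 and 0.431, again a loss of about 2% to 14%. With a true difference of zero, or with exclusion unrelated to the result, the bias is about zero.

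**Scale.** With 36 per arm (45 × 0.80) the standard error of the difference is √(2/36) = 0.236 SD. The largest loss in the worst-case table is 0.20 − 0.122 = 0.078 SD, about a third of one standard error.

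**The case against.** The strongest reply is that this concerns an optional, supplementary analysis in an exploratory pilot. That stands: the main efficacy analysis uses the full analysis set, whose definition does not depend on week 12. It sets the severity.

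A second reply is that one strict completer set for all visits is a legitimate choice, because laboratory tests are taken at week 12 and Section 2.12 plans a repeated-measures comparison across visits. That justifies requiring week 12 for analyses that use week 12 data. It gives no reason to require it for a week 8 outcome.

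A third is that the full protocol or analysis plan, not shown, may define completion and significant violations. It may. The point here is not missing detail, however: the article states a completion rule, goes as far as a 70% compliance cut-off, and the rule as stated does not match the endpoint.

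A reader might go further and infer that participants are removed because of their week 8 result, so that the worst responders are trimmed. The article does not support this. It does not say that week 8 lipids are disclosed to participants or acted on. The prohibited list in Section 2.5 does not name statins, which the Introduction calls first-line. Only significant violations exclude, and a drug started after the endpoint draw need not be judged significant. No rate of starting a listed drug in weeks 8 to 12 is given, so the 5–20% used above is assumed.

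**Conclusion.** The point holds as a minor mismatch between an analysis-set rule and the endpoint it serves. On the literal text, a compliant participant with a valid week 8 LDL-C leaves the per-protocol analysis for missing an off-drug visit four weeks later; a drug started after the draw may have the same effect.

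The loss of participants with usable data follows from the wording whenever someone misses week 12. Its size, about 4% in standard error, rests on evenly spread dropout. Attenuation is conditional on exclusions being related to the week 8 result: roughly 2–14% under partial uptake, 17–39% under a sharp threshold, which is a worst case. With the same rule in both arms it acts towards no effect and creates no apparent benefit when there is none. The inference that the trial's main result is at risk is not supported, since the full analysis set is untouched.

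**What to change.** In Section 2.12, add that for week 8 outcomes the per-protocol set is defined by events up to the week 8 blood draw: week 8 LDL-C obtained, at least 70% compliance, and no significant violation between randomisation and that draw. State that a missed week 12 visit, or a medication change after the week 8 draw, does not remove a participant from these analyses. Require week 12 completion only for per-protocol analyses of week 12 data.

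This costs a sentence or two in the analysis-set definition, best settled before unblinding. It needs no new data, visits or participants, and leaves the conduct rules in Section 2.5 as they are.

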### 2.9. Randomization and allocation concealment

An independent statistician will generate a random assignment code using the block randomization method with block sizes in SAS® Version 9.4 (SAS Institute Inc., Cary, NC). Participants who satisfy the eligibility criteria will be assigned to the GBH or placebo granule group at the baseline visit (week 0) with a 1:1 allocation ratio. The generated code will be sealed in opaque envelopes and stored in double-locked cabinets. We will maintain allocation concealment throughout the study period by providing participants with identically packaged, consecutively numbered drug containers.

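### Baseline-adjusted ANCOVA is written only for LDL-C; the between-arm analysis of the secondary outcomes is either unadjusted or not clearly assigned

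*Protocol article*

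**What the plan says.** All of the following is in section 2.12 of the protocol article unless another section is named.

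- **Primary outcome.** The text reads "The primary outcome of this study is the mean change in LDL-C levels from baseline to week 8". The next sentence gives the test, "A 2-sided test with a significance level of 5% will be performed", and the model, "analysis of covariance with baseline as the covariate and the treatment group as the fixed factors". No other outcome is named with this model.
- **General rule for continuous data.** "Continuous data will be analyzed using the independent t-test or Wilcoxon rank-sum test". This closes the paragraph that opens with demographic and general clinical characteristics. The paragraph on the primary outcome comes after it.
- **Other analyses of outcomes.** "The intragroup changes in outcome measures from baseline to posttreatment will be analyzed using the paired" t-test or the signed-rank test, and "repeated-measures analysis of variance will be used to compare the differences in trends between visits in each group".
- **Secondary outcomes (section 2.6.2).** Percentage changes in TC, HDL-C, TG and apolipoproteins A1 and B to week 8, other blood lipid parameters, and change in the blood stasis total score.
- **Centres.** "Subjects will be recruited from 2 hospitals" (section 2.1). Allocation is made "using the block randomization method with block sizes" (section 2.9), with no statement on stratification by hospital. No analysis names hospital.

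**The concern.** Each named secondary outcome is a change from a pre-treatment value, so a covariate that predicts it is already being collected. A between-arm test on change that leaves this covariate out has a wider interval than necessary.

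Entry under section 2.3.1 needs only one or more of four lipid abnormalities. A patient may therefore be normal or clearly abnormal on any single lipid, and baseline values will be spread out. Percentage change has the baseline value in its denominator, so that spread enters the outcome directly.

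The secondary estimates matter here. The Introduction says that earlier studies differ on which lipid the product affects, and the Discussion says that a confirmatory trial will be designed from these results. If the between-arm method is left open, a choice among a t-test, a rank test, ANCOVA and repeated-measures ANOVA could be made after the data are seen.

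**Working it through.** **1. Evaluable patients.** Section 2.8 gives 45 per arm and 20% dropout: 45 × 0.80 = 36 per arm. The stated 90 is reproduced by a pilot-precision rule with effect size 0.20 and an assumed one-sided 80% confidence level: 2 × (0.8416/0.20)² = 35.4, rounded up to 36; 36/0.80 = 45; 2 × 45 = 90. The article states no confidence level. The fix does not change this figure.

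**2. Which stated methods compare arms on a secondary outcome?**

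| Method in section 2.12 | Compares arms? | Adjusts for baseline? | Assigned to secondary outcomes? |
|---|---|---|---|
| ANCOVA | yes | yes | no; follows the LDL-C sentence |
| t-test or rank-sum | yes | no | unclear; in the participant characteristics paragraph |
| Paired t or signed-rank | no | not applicable | yes, within arm only |
| Repeated-measures ANOVA | unclear | none stated | unclear |

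Even if the repeated-measures ANOVA is meant to compare arms, it does not supply the adjustment. With baseline as one of two visits, its group-by-visit test is the same as the t-test on change.

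**3. Size on the change scale.** Assume equal variance σ² at both visits and correlation ρ. The per-patient variance is 2σ²(1 − ρ) for the unadjusted change and σ²(1 − ρ²) for ANCOVA. The ratio is (1 + ρ)/2.

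| ρ (assumed) | Variance ratio | SE ratio | Unadjusted n per arm for equal precision (36/ratio) |
|---|---|---|---|
| 0.4 | 0.70 | 0.837 | 51.4 |
| 0.6 | 0.80 | 0.894 | 45.0 |
| 0.8 | 0.90 | 0.949 | 40.0 |
| 0.9 | 0.95 | 0.975 | 37.9 |

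**4. Size on the percentage-change scale.** Simulation with lognormal values, 36 per arm and coefficients of variation from 0.15 to 0.4 gave ANCOVA to t-test variance ratios of 0.71 to 0.79 at correlation 0.4, 0.81 to 0.84 at 0.6, and 0.91 to 0.92 at 0.8. Allowing for variation between runs, the reduction is about 7% to 29%. As interval width, √0.93 = 0.964 and √0.71 = 0.843, so intervals would be about 4% to 16% narrower.

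**5. Power, as an illustration.** Take an effect of 0.66 SD of the change score, which the unadjusted test detects with 80% power: 0.66 × √(36/2) = 2.80, and Φ(2.80 − 1.96) = 0.80. With ANCOVA:

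- ρ = 0.8: Φ(2.80/0.949 − 1.96) = 0.84
- ρ = 0.6: Φ(2.80/0.894 − 1.96) = 0.88

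**6. Hospital.** Assume an equal split of patients and a between-hospital difference of d residual SDs. Adding the term multiplies the SE by 1/√(1 + d²/4), a gain of 0.1% (d = 0.1), 0.5% (0.2), 1.1% (0.3) or 3.0% (0.5). The cost is one residual degree of freedom: 72 − 3 = 69 becomes 68.

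Without stratification, the between-arm difference in hospital share has an SD of about √(0.25 × 2/45) = 0.105. At d = 0.3 the typical shift is 0.105 × 0.3 = 0.03 SD, against a standard error of √(2/36) = 0.24 SD. If blocks were run within hospital and the term left out, the 5% test would be slightly conservative: 0.0497 at d = 0.1 and 0.0434 at d = 0.5.

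**The case against.** The strongest reply is that a reader might infer from section 2.12 that the secondary outcomes will definitely be tested without adjustment, and the text does not say so. The t-test sentence belongs to the paragraph on participant characteristics, and nothing expressly limits ANCOVA to LDL-C. A condensed article may leave secondary models to an analysis plan that is not shown. This stands, and it is why the precision loss is stated conditionally. It does not remove the point. The article sets out a general rule and a specific model and ties the model to one outcome, so a reader cannot tell which method applies to the rest.

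A reader might also infer that the test will be picked by inspecting the data. The article links the data distribution to how results are presented (mean or median) and gives no rule for choosing the test.

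On hospital, a reader might infer that leaving it out biases the primary estimate. It does not. Under 1:1 randomisation the estimate is unbiased, and chance imbalance is already reflected in the standard error. Silence on stratification in an article does not show that there was none. Omitting centre with two hospitals is a defensible choice.

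Finally, every correlation, coefficient of variation and SD used here is assumed. At correlation 0.8 the gain is small, and other assumed means and SDs gave variance ratios of 0.93 to 0.98. The lower end of the range is therefore soft. No single power figure can represent five analytes and a questionnaire score.

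**Conclusion.** The point holds as one of precision and clarity. A baseline-adjusted between-arm analysis is written for LDL-C alone; for the secondary outcomes the method is either unadjusted or not clearly assigned. If it is unadjusted, ANCOVA would reduce the variance of the percentage-change comparison by about 7% to 29%. This rests on 36 evaluable patients per arm and assumed correlations of 0.8 down to 0.4, none of which the article supplies.

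The article does not support a claim of bias or of an invalid primary test: the primary analysis is already baseline-adjusted. The hospital term is a minor matter, worth about 0.1% to 3% in standard error for an assumed between-hospital difference of 0.1 to 0.5 SD.

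**What to change.** State that TC, HDL-C, TG, apolipoprotein A1, apolipoprotein B and the blood stasis score are each compared between arms by the same ANCOVA as LDL-C, with arm and that outcome's own baseline value, and that the Wilcoxon test is a sensitivity check only. Say whether the t-test and rank-sum sentence applies only to participant characteristics, and whether the repeated-measures ANOVA compares arms.

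As a minor addition, include hospital as a fixed factor in these models, or say why it is left out, and state whether blocks were run within hospital. If they were, the term also matches the analysis to the design. A log ratio for TG and a list of imputation-model variables are optional and not needed to resolve this point.

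The cost is a few sentences in the analysis plan, settled before unblinding, and one degree of freedom for hospital. No new data and no change to the sample size of 90 are needed.

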### 2.8. Sample size calculation

This is a preliminary exploratory study to assess the clinical effect and safety of GBH on serum lipid levels and CV risk in patients with borderline hyperlipidemia. According to a study that recommended the minimum sample size for the preliminary study,^[25]^ the minimum effect size was assumed to be 0.20, a dropout rate of 20% was considered, and a total of 90 participants (45 in each group) are set as the target sample size.

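### The tests named for within-arm change in dichotomous variables ignore the pairing; a minor wording error, because no listed measure is defined as dichotomous

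*Protocol article*

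**What the plan says.** Section 2.12 (Statistical analysis) of the protocol article introduces the within-arm analysis with "The intragroup changes in outcome measures from baseline to posttreatment will be analyzed using the paired" *t* test, and continues with "Wilcoxon signed-rank test for continuous variables and the chi-square test or Fisher exact test for dichotomous variables". The sentence therefore concerns one group seen at two times.

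The paragraph before it deals with the general comparison of data. There the independent t-test and the Wilcoxon rank-sum test are given for continuous data, and "dichotomous data will be analyzed using the chi-square test or Fisher exact test".

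The primary analysis is separate: "A 2-sided test with a significance level of 5% will be performed using an analysis of covariance", with baseline as covariate and treatment group as factor. The article nowhere names McNemar's test or any other test for paired binary data.

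**The concern.** Each participant contributes two linked observations to a within-arm comparison. The paired t test and the signed-rank test respect that link. Pearson's chi-square and Fisher's exact test assume independent observations, and there are two ways to apply them here, both wrong for this question:

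- **Stack the visits** as if baseline and post-treatment were two separate groups. The standard error then leaves out the within-person covariance. With positive correlation the test is too conservative and loses power; with negative correlation it rejects too often.
- **Cross-tabulate baseline by post-treatment.** The test then asks whether the two visits are associated. They usually are, even when nothing has changed.

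At stake is the p-value for any binary before-and-after result reported within an arm. A conservative test could, for example, hide a shift in a laboratory value classed as normal or abnormal. That classification is an assumption; the article does not say it will be made.

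**Working it through.** **The text, side by side.** Between the two paragraphs of section 2.12 the continuous tests change from independent (t-test, rank-sum) to paired (paired t, signed-rank). The dichotomous tests stay the same, chi-square or Fisher. The unpaired pair was carried over into the paired setting.

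**Inputs from the article.** "a total of 90 participants (45 in each group) are set as the target sample size" and "a dropout rate of 20% was considered" (section 2.8). Hence 45 × (1 − 0.20) = 36 completers per arm, which is inferred and not stated. The 5% two-sided level is stated for the primary analysis and assumed for the within-arm tests. The article gives no figure on this point to reproduce.

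**Assumed, not in the article.** Prevalence 50% at both visits under no change; a fall from 50% to 30% as the alternative; latent (underlying normal) within-person correlation ρ of 0.5, 0.7 and 0.85.

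**Formula.** With n pairs, prevalence p at both visits and binary correlation φ, the variance of the difference in proportions is 2p(1−p)(1−φ)/n. The stacked chi-square uses 2p(1−p)/n. Its z statistic therefore has standard deviation √(1−φ) instead of 1, and the true rejection rate is about 2 × P(Z > 1.96/√(1−φ)). The sample size cancels.

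At 50% prevalence φ = (2/π)·arcsin(ρ), which gives 0.333, 0.494 and 0.647:

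- ρ = 0.5: 1.96/√0.667 = 2.40, about 1.6%
- ρ = 0.7: 1.96/√0.506 = 2.76, about 0.6%
- ρ = 0.85: 1.96/√0.353 = 3.30, about 0.1%

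For φ = −0.3 the same formula gives 1.96/√1.3 = 1.72, about 8.6%, so the direction of the error depends on the sign of the correlation.

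**Simulation, n = 36, percentage of samples rejected:**

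| | ρ = 0.5 | ρ = 0.7 | ρ = 0.85 |
|---|---|---|---|
| No change: stacked chi-square | 1.5 | 0.6 | 0.2 |
| No change: McNemar, asymptotic | 4.4 | 4.5 | 4.3 |
| No change: McNemar, exact | 2.5 | 1.9 | 1.4 |
| No change: Fisher on baseline-by-post table | 45 | 82 | 99 |
| 50% to 30%: stacked chi-square | 40 | 39 | 36 |
| 50% to 30%: McNemar, asymptotic | 53 | 63 | 77 |
| 50% to 30%: McNemar, exact | 43 | 53 | 65 |

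**One invented data set, n = 45.** Suppose 20 participants are positive at both visits, 10 at neither, 12 only at baseline and 3 only afterwards. The marginal counts are 32 and 23 of 45.

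- Stacked chi-square: p = 0.052; stacked Fisher: p = 0.083.
- Asymptotic McNemar: (12 − 3)²/(12 + 3) = 81/15 = 5.4, p = 0.020.
- Exact McNemar: 2 × (1 + 15 + 105 + 455)/32768 = 1152/32768, p = 0.035.

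**The case against.** **No listed measure is dichotomous.** The primary outcome is "Percentage changes in LDL-C from the baseline to week 8". The secondary outcomes are percentage changes, lipid parameters and a questionnaire score; the exploratory outcome is a metabolite analysis; the before-and-after safety tests in section 2.7 are continuous laboratory values. The blinding guess has three categories, is asked once and has its own index. The clause bites only on a variable derived or categorised later. This stands, and it sets the severity.

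**The illustration can be read too strongly.** Exact McNemar is itself conservative. The expected number of discordant pairs under no change is 36 × 0.5 × (1 − φ), or about 12, 9 and 6, so the exact version may well be the one used. At ρ = 0.5 its power is only 3 points above the stacked chi-square (43% against 40%), and its error rate (2.5%) is not far from 1.5%. The Fisher rejection rates of 45% to 99% arise only if the visits are cross-tabulated and association is read as change; the article does not say this will be done. At 10% prevalence that range is roughly 18% to 58%. Because missing values are to be imputed, the analysed number may also be nearer 45 than 36. All of this stands as a limit on size. None of it makes the named tests valid.

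**Chi-square might mean McNemar's chi-square.** This fails: it is coupled with Fisher's exact test, and the same couple serves the unpaired comparisons.

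**The detail belongs to the analysis plan.** This fails too. The article does not leave the test open; it names the wrong one.

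**Conclusion.** Wrong as written, and minor. The named tests are invalid for paired binary change whatever the sample size; only the size of the error depends on the assumed prevalence and correlation. Under the assumptions above, the stacked chi-square holds about 1.5% to 0.2% instead of 5%. It gives up between 13 and 41 points of power against asymptotic McNemar (53 − 40 and 77 − 36), or 3 to 29 points against exact McNemar (43 − 40 and 65 − 36).

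A reader might infer that the trial's efficacy conclusion is at risk. The documents do not support that: the primary inference is a between-arm covariance analysis of a continuous outcome, the trial is described as an exploratory pilot, and neither the sample size nor any planned decision uses this clause. Nor does the article say that within-arm tests will be taken as evidence of a treatment effect, so a demand to relabel them as descriptive does not follow from this error.

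**What to change.** In the within-arm sentence of section 2.12, and in the analysis plan where it repeats that sentence, replace the two tests named for dichotomous variables with: McNemar's test, in its exact form when discordant pairs are few. Keep chi-square and Fisher's exact test for comparisons between arms. The cost is one line of wording; no data collection, sample size or primary analysis changes.
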